#### Visual Analogue Scale (VAS)

The VAS for pain assessment is widely used in China. The basic method is to use a 10-cm-long swimming ruler which has ten-scale on one side and the two ends of the ruler are with the digits 0 and 10. “0 point” indicates no pain, and “10 point” represents the most severe pain which is unbearable. During the assessment, the scaled side is faced back to the patient, and the patient marks on the ruler with the scale points that represents his or her pain level, and the physician records the score based on the position marked by the patient.

#### Measurement of range of joint motion (ROM)

The degree of mobility of the shoulder joint was measured using the American muscle strength test and the joint mobility meter (portable) (Hoggan MicroFET3). This study will measure the angle of the shoulder flexion, extension, abduction, internal rotation, and external rotation.

### Secondary outcome

#### Measurement of pressure pain threshold (PPT) and pressure pain tolerance (PTT)

This study will be performed using the FDK20 handheld pressure an algeometer manufactured by Wagner Instruments, USA. The device measures the individual’s pain sensitivity by applying pressure which includes measuring the pressure pain threshold (PPT) and the pressure pain tolerance (PTT). Initially, the data that will be transferred to the tester when the subject just felt pain, which will be recorded as PPT. Furthermore, after a short pause, the pressure will be increased until the pain becomes intolerable to the subject. After a short pause, the tester may increase the pressure until the patient feels that the pain caused by this pressure is intolerable. When the patient informs the tester for the second time, the tester will record it as PTT. The test value of the pain indicator is only visible to the tester during the whole process. The tester sequentially measures the pain threshold and pain tolerance threshold of the patient’s marked points, and the test interval for different points is 5 min. The data will be analyzed in units of kg/cm^2^.

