### Group A: stuck-moving needle acupuncture MTrp treatment group

#### Selection and positioning method of shoulder joint myofascial trigger pain points

The selection of shoulder joint myofascial trigger pain points will be achieved by a dynamic search. Further, patients will be subjected to do three actions including the first one as abduction, lifting, and touching the head. The second one is forward flexion and internal rotation by touching the opposite shoulder. The third one is a posterior extension and touching patient’s back. These three actions can indicate the patient’s pain area. At the same time, the doctor will use his or her thumb to press these areas and confirms the muscle tension band. The compression can lead to localized pain and muscle spasm and strengthen the stimulation to induce the mentioned pain. Once the pain is induced, the doctor will ask the patient if the pain is similar to what he or she usually feels. If the pain is similar to the pain patient usually feels, then the doctor will place a pressure manometer on the main tenderness point to evaluate the pain point. Further, by placing the pressure manometer (Wagner Instruments, USA, specification model: FDK20) at the pain area, slowly pressure will be applied. Using this equipment, doctor can measure the tenderness threshold and can remove the pain points below the tenderness threshold of 2 kg/cm^2^. After locating the pain points, the doctor will use a black pen to draw “×” on it.

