### Group B: common acupuncture control group

#### Acupoints

Jianyu (LI15), Jianliao (TE 14), Jianzhen (SI 9), Biru (LI14), Ashi points.

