## Outcomes

The following outcomes will be assessed by independent outcome assessors. These assessors will be trained before participating in this trial and unaware of the group assignments. The outcome assessments will be performed at four time points including at the baseline, at the end of the stuck-moving needle acupuncture treatments, in the 4-week follow-up period, and at the end of the follow-up period.

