The needle application site is a key factor that affects the effect of acupuncture. In this study, the operation site of the stuck-moving needle is the localized MTrp of the shoulder joint. Studies in recent years have found that the occurrence of frozen shoulders is often related to the muscles around the shoulder joint related to the pain points [34, 35]. These muscles include deltoid muscle, biceps, pectoralis major, pectoralis minor, and coracobrachialis muscle. These points of muscle are common, and it can cause pain and impair shoulder movement. If it can be accurately positioned in clinical treatment for effective treatment, the effect will be greatly improved. The pain points of the affected muscles of the shoulder joint are characterized by tenderness, which restricts the complete extension of the muscles, causing muscle weakness, and can be directly compressed to conduct the patient’s identifiable pain, whereas sufficient stimulation can cause twitch response. Based on the characteristics of MTrp with tenderness and referred pain [36], we used a pain meter to determine the location of the local pain points in the shoulder joint and then performed a stuck-moving needle operation with a marker to ensure the accuracy of the operation. During this study, we used patented stuck-moving needles termed as Li Zhenquan’s needles, produced by Suzhou Acupuncture Supplies Co., Ltd., with a size of 0.4 × 40 mm.

The stuck-moving needle acupuncture method can increase the stimulation intensity, breadth, and depth of acupuncture. It is applied to the Trp for the localized activation of the shoulder joint, making the local capillaries of the Trp quickly contract and relax, improve the state of local tissue microcirculation, and accelerate the local metabolism. At the same time, by increasing the intensity of acupuncture, it can increase the rapid release of certain analgesics in the pain point. This relieves pain symptoms.

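### PPT and PTT are measured at marked points, but locating and marking points is described only as a group A treatment step, so the three-arm comparison has no common stated site

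*Protocol article*

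**What the plan says.** All references are to the protocol article.

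- **Outcome definition** (Measurement of pressure pain threshold (PPT) and pressure pain tolerance (PTT)): "The tester sequentially measures the pain threshold and pain tolerance threshold of the patient’s marked points". The section names the FDK20 gauge, the order of the two readings, a 5-minute interval between points and the unit. It gives no other rule for the site and does not restrict the phrase to one arm.
- **Group A** (first subsection, on choosing and positioning the trigger points): the step opens with the statement "The selection of shoulder joint myofascial trigger pain points will be achieved by a dynamic search". Thumb palpation follows, then a reading on an FDK20 gauge, with which the doctor "can remove the pain points below the tenderness threshold of 2 kg/cm"². The marking comes next: "After locating the pain points, the doctor will use a black pen to draw" a cross on each. The Discussion links this step to the needling: "we used a pain meter to determine the location of the local pain points in the shoulder joint".
- **Group B** (Acupoints; Method of operation): "Jianyu (LI15), Jianliao (TE 14), Jianzhen (SI 9), Biru (LI14), Ashi points". Acupoints are located by a national standard. No gauge screening and no ink mark are described.
- **Group C** (physical exercise control group): exercise only, with no points.
- **Assessors** (Outcomes): "These assessors will be trained before participating in this trial and unaware of the group assignments". Assessments are at baseline, end of treatment, 4-week follow-up and end of follow-up.
- **Analysis** (Statistical analysis): primary and secondary outcomes are compared by analysis of variance.

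**The concern.** A pressure threshold depends on where the gauge is placed. A between-group comparison of PPT or PTT is interpretable only if the sites are chosen by the same rule in each arm, independently of allocation. Here the outcome refers to marks whose only described origin is one arm's treatment procedure. Three things are at stake.

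1. **Comparability.** Tender trigger points in group A could be set against acupoints, unspecified points or nothing in groups B and C.
2. **Selection on the outcome.** The group A points are kept or dropped on a pressure reading from the same gauge model. No such rule is described for the other arms.
3. **Assessor blinding.** A cross on the shoulder, or the presence of marked points to test in one arm only, could tell the PPT/PTT assessor who is in group A.

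**Working it through.** The plan states no figure for this point, so the check is mainly a comparison of sections.

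**Step 1: is there a site rule for each arm?**

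| Arm | Patients planned | Points located by | Gauge screening | Mark |
|---|---|---|---|---|
| A | 36 | movement search and palpation | 2 kg/cm² rule | black cross |
| B | 36 | national acupoint standard; Ashi points, method not stated | none described | none described |
| C | 36 | none described | none described | none described |

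The outcome refers to marked points, and a mark is described in one row. For the other two rows, 36 + 36 = 72 of 108 patients, the article states no procedure that produces the points to be tested.

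**Step 2: does the timing fit?** Outcomes are also taken at baseline, before the 3-week treatment period. If marking belongs to group A treatment, it comes after allocation, and a baseline reading at marked points is not possible even in group A. If marking is done at baseline, it must be done before anyone knows who is in group A, and so in everyone; no section says this. Either way the two sections do not fit together as written.

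**Step 3: what would one-arm screening do?** The documents give no PPT mean, SD or retest correlation. The following are assumptions for illustration: mean μ = 2 to 3 kg/cm², SD σ = 0.7 to 1.0, retest correlation r = 0.70 to 0.85. The screening wording can be read in two directions, so both are shown. With z = (2 − μ)/σ and φ, Φ the standard normal density and distribution function:

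- Shift in level if points at or above 2 are kept: σ·φ(z)/(1 − Φ(z)). For μ = 2, σ = 1: 0.399/0.5 = 0.80 kg/cm² upward. Range about 0.1 to 0.8.
- Shift if points below 2 are kept: σ·φ(z)/Φ(z). For μ = 3, σ = 1: 0.242/0.159 = about 1.53 kg/cm² downward. Range about 0.6 to 1.5.
- Drift back on retest with no treatment effect: (1 − r) × shift. First reading: 0.30 × 0.80 = 0.24 kg/cm², range 0.02 to 0.24, a fall. Second reading: 0.30 × 1.53 = 0.46, range 0.08 to 0.46, a rise.

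These are shifts in the reading used for screening. The drift enters change from baseline only if that reading is also the baseline outcome value. If an assessor takes a separate baseline reading after screening, the drift falls between screen and baseline, and change from baseline is not biased by this mechanism. A difference in level between group A and the other arms can remain.

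**Step 4: when could the assessor learn the allocation?** This needs either a treatment mark still visible at an assessment, or marked points to test in group A only. For range of motion (ROM), a primary outcome, the person measuring it would also have to see the mark.

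**The case against.** The strongest reply is that marking is described only for group A, which is not the same as being done only in group A. The outcome section has no arm restriction. The abstract gives a 1-week baseline period, and the Confidentiality section mentions pain threshold measurement for patients generally. The schedule table and trial flow figure are not shown, and the Quality control section says the pain tester is used under standard operating procedures. Points may therefore be marked in every patient at baseline. This stands as a limit: a reader might infer that groups B and C are certainly unmarked, and the documents do not establish that. It does not remove the point, because no section states universal marking. The site is also not detail left out of a condensed article: it is stated, by reference to something described in one arm only.

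Two further objections stand in full.

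- A reader might take the drift figures as the bias in the trial. They rest on assumed inputs, their sign depends on how the screening wording is read, and they require the screening reading to serve as baseline. The article has a doctor screen the points and independent assessors measure outcomes, so that condition may well not hold.
- A reader might conclude that blinded ROM assessment is compromised. The skin is cleaned with 75% alcohol before needling, nothing says that ink persists to an assessment, and by the 12-week follow-up a treatment mark would have to be redrawn. No section says that the PPT/PTT tester also measures ROM.

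**Conclusion.** The point holds as a defect in how two secondary outcomes are defined. As written, the three-arm comparison of PPT and PTT has no common measurement site, because the article describes a locating-and-marking step for group A alone and none for the other 72 of 108 planned patients. That conclusion rests on the text and needs none of the assumed values.

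The consequences are conditional. If the group A treatment points are the outcome sites, group A's PPT level can be shifted by selection on the outcome scale. Bias in change from baseline needs the screening reading to double as baseline, and its size and sign cannot be determined from the documents. The PPT/PTT assessor could learn the allocation if a mark remains visible or if only group A has points to test; ROM is affected only if the same assessor sees the mark. VAS, on which the sample size rests, does not use marked points. The change should be made, but the point does not by itself undermine the primary outcomes.

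**What to change.** Reconcile the PPT/PTT outcome section with the group A point-selection section:

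1. Locate the PPT/PTT sites by the same search in all 108 patients during the baseline week, before the allocation envelope is opened, without selecting outcome sites on their PPT value.
2. Record the coordinates of the sites on the CRF.
3. Measure the same sites in all three arms at all four assessments, with a baseline reading separate from any screening reading.
4. At assessment, mark all arms identically, or leave no treatment mark visible to the assessor.
5. Analyse one value per patient, the mean over that patient's recorded sites.

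The selection of treatment points in group A need not change. If marking every patient at baseline is already intended, the revision mainly states this and keeps the outcome sites free of the gauge screening. The cost is one protocol paragraph and a few extra minutes per group B and C patient at baseline, with a gauge already in use.

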#### Oxford Shoulder Score (OSS)

The OSS consisted of 12 questions. These questions were related to the pain (1~4 questions) and functional activities (5~12 questions). There are five alternative answers for each question. The best case is 1 point, the worst is 5 points, and the total score will be between 12 and 60 points. The higher the score, the worse the shoulder function will be.

#### Short form-36 questionnaire (SF-36)

The quality of life assessment scale includes 36 questions, which are related to the general health problems, physical function problems, limitations of daily life due to physical strength and physical pain, social skills, psychological repression and well-being, and functional limitations caused by emotional problems.

#### Evaluation of patient’s satisfaction

Based on the present study, this scale will provide medical services to patients, which will allow evaluation of treatment in a true and objective manner.

### Sample size estimation

According to the previous researches, the difference between the VAS score before and after treatment in the general acupuncture group was 4.7, with a standard deviation of 1, whereas the difference in VAS score before and after treatment in the functional exercise group was 3.5, with a standard deviation of 1 [14]. In combination with the pilot experimental results from this study, the VAS score before and after treatment of frozen shoulder patients with stuck-moving needle acupuncture dropped by 5.2 and the standard deviation was 1.06. This study was a prospective study with three groups and the sample size as 1:1:1. The sample size was calculated using *F*-test in software SAS 9.4, and we used single-factor analysis of variance to calculate the sample size. The test level was set at *α* = 0.05, β = 0.1, and the test efficiency was set at 1 − *β* = 0.9. The results showed that the test power was 0.931, and the number of samples in each group was not less than 30. By considering the problem of missing samples or losing to follow-up, the sample size will be increased by 20. This means that the minimum sample size of each group will be 36 patients, and finally, the total sample of the three groups will include cases not less than 108.

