### Main outcome indicators

The primary evaluation index in the trial will be the change involved in the scores on the Visual Analogue Scale (VAS) and measurement of range of joint motion (ROM) from the baseline period through the 12 weeks of the follow-up period.

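### The stated power of 0.931 rests on undated before/after-treatment VAS changes and is not shown to apply to the primary outcome, change in VAS and ROM to the 12-week follow-up

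*Protocol article*

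**What the plan says.** Under Sample size estimation, the protocol article takes three inputs:

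- common acupuncture: "According to the previous researches, the difference between the VAS score before and after treatment in the general acupuncture group was 4.7", with an SD of 1;
- exercise, from the same source: "the difference in VAS score before and after treatment in the functional exercise group was 3.5, with a standard deviation of 1";
- stuck-moving needle, from the team's pilot: VAS "dropped by 5.2 and the standard deviation was 1.06".

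The method is a three-group F-test: "we used single-factor analysis of variance to calculate the sample size". The error rates are given as "The test level was set at *α* = 0.05, β = 0.1". The result is "The results showed that the test power was 0.931" with at least 30 per group, raised to 36 per group and 108 in total to allow for losses.

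Under Main outcome indicators, the primary outcome is the change in VAS and ROM "from the baseline period through the 12 weeks of the follow-up period"; the Abstract also places it at the 12-week follow-up. The opening of the Outcomes section lists end of treatment, the 4-week follow-up and the end of follow-up as separate assessments. The Discussion puts the last visit 12 weeks after treatment ends. Treatment itself lasts 3 weeks.

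**The concern.** The power statement and the primary outcome are not tied to the same time point. The inputs describe change over treatment. The outcome runs to a visit 12 weeks after treatment has stopped. No sentence says that the inputs were measured that late, or that the differences and SDs are expected to hold until then.

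Persistence cannot be taken for granted. The Background calls the condition self-limiting, and the Discussion mentions both self-healing and a high chance of recurrence. Recovery under exercise or relapse after needling would shrink the differences, and a mix of the two could widen the SD. ROM is named beside VAS as a primary measure but does not enter the calculation.

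At stake is how the result is read. A null finding at 12 weeks would be judged against a claim of 90% power or more that was not derived for that outcome.

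**Working it through.** **Inputs (Sample size estimation).** Mean VAS falls 5.2, 4.7 and 3.5; SDs 1.06, 1 and 1; α = 0.05; three equal arms of 30, or 36 after inflation. Pooled SD = √[(1.06² + 1² + 1²)/3] = 1.02.

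**Formula, overall test.** Noncentrality λ = n × Σ(mean − grand mean)² / SD². Power is the probability that a noncentral F with 2 and 3(n − 1) degrees of freedom and noncentrality λ exceeds the 5% critical value.

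Grand mean = (5.2 + 4.7 + 3.5)/3 = 4.467. Sum of squares = 0.733² + 0.233² + 0.967² = 1.527.

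**Step 1: the plan's own figure.** At n = 30 and SD 1.02, λ = 30 × 1.527/1.0404 = 44.0 and power is above 0.999. The same holds for SD 1.00 and SD 1.06. The printed 0.931 does not reproduce. Two ways of getting close to it:

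- 10 per arm gives 0.921 at SD 1.00; 11 per arm gives 0.946, 0.938 and 0.918 at SD 1.00, 1.02 and 1.06. A total of about 30 read as a per-group number would explain this, but that is inference.
- 30 per arm gives 0.931 only if the SD is about 1.77, which the document does not state.

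The inflation does reproduce if the stated 20 is read as a percentage: 30 × 1.2 = 36 and 3 × 36 = 108.

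**Step 2: the 12-week outcome.** The document gives no week-12 means or SDs, so no single figure exists. Assume that a fraction r of the arm differences remains; then λ is multiplied by r². For example, r = 0.5, n = 30, SD 1.02 gives λ = 44.0 × 0.25 = 11.0.

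| Assumed share remaining | Assumed SD | Power, 30 per arm | Power, 36 per arm |
|---|---|---|---|
| all | 1.02 | >0.999 | >0.999 |
| half | 1.02 | 0.84 | 0.90 |
| half | 1.5 | 0.50 | 0.58 |
| one third | 1.02 | 0.48 | 0.56 |

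At 30 per arm, power falls below 0.9 when less than about 53% (SD 1.00) to 57% (SD 1.06) of the differences remain or, with the full differences kept, when the SD exceeds about 1.87.

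**Step 3: stuck-moving needle versus common acupuncture, stated inputs, no attenuation.** Difference = 5.2 − 4.7 = 0.5. Two-sample noncentrality = 0.5/(SD × √(2/n)). At SD 1.02 this is 1.90 at n = 30 and 2.08 at n = 36, giving two-sided power of 0.46 and 0.54. Over SD 1.00 to 1.06 the ranges are 0.44–0.48 and 0.51–0.55.

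**Step 4: ROM.** There is nothing to recompute. The document gives no ROM difference, SD or power.

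**The case against.** The strongest reply has four parts.

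- **The inputs are undated.** The phrase about before and after treatment carries no date for the cited study or the pilot, so calling the inputs end-of-treatment values goes beyond the text. This stands. It limits the point to power that is not shown to apply; it does not prove that the inputs are wrong at week 12.
- **The endpoint wording is loose.** The primary outcome runs through the follow-up, four assessments are planned, and Statistical analysis also plans a three-group comparison before and after treatment. A reading in which change at the end of treatment belongs to the primary outcome is therefore open. This stands in part: the Abstract speaks of change from baseline to the 12-week follow-up, and on either reading the 12-week change is included while the calculation does not address it.
- **The overall test has wide slack.** With 60% of the differences left and SD 1.06, power at 30 per arm is still 0.931; with half left and SD 1.02 it is 0.90 at 36 per arm. This stands. A reader might infer that the trial is underpowered at 12 weeks, but the documents do not support that: a marked shortfall needs an assumed loss of about two thirds, or halving together with a larger SD, and the text gives neither figure.
- **The low pairwise power is a separate matter.** This also stands. The 0.46/0.54 arises at the stated inputs, from sizing on an omnibus test, and does not measure the effect of the time point.

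None of this supplies the missing link to week 12, a calculation for ROM, or a derivation of 0.931.

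**Conclusion.** The concern holds as a gap between the calculation and the primary outcome. The target of 0.9 and the printed 0.931 come from undated before/after-treatment VAS changes; the primary outcome is change in VAS and ROM to the 12-week follow-up. Nothing bridges the two, and ROM is not covered.

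For 12-week VAS change, the overall test at 30/36 per arm runs from above 0.999 if everything persists to 0.48/0.56 if one third remains, both at SD 1.02. With half remaining it is 0.84/0.90 at SD 1.02 and 0.50/0.58 at SD 1.5. The retained shares and the SD of 1.5 are assumptions.

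Two results need no assumption about persistence: 0.931 is not the power at 30 per arm on the stated inputs, and the comparison of the two needling methods, which the article's aims put first, has power near one half. It should be corrected, because it affects how a null result would be read. It does not call the design or the enrolment into question.

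**What to change.** Under Sample size estimation:

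1. State when the before/after-treatment changes were measured, for both the cited study and the pilot.
2. Replace 0.931. Simply labelling it as power at the end of treatment would keep a wrong number, since the stated inputs give above 0.999 at 30 per arm.
3. Give power for 12-week VAS change over stated assumptions on the remaining differences and the SD, as in the table above, set without reference to unblinded data.
4. Say that the figure covers VAS only and that ROM was not used in sizing.
5. State separately that stuck-moving needle versus common acupuncture has power of about 0.46/0.54 at 30/36 per arm on the stated inputs (SD 1.02), as a consequence of sizing on the three-group test.

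Keep the 12-week primary time point. Moving it to match the calculation is hard to defend once enrolment has begun, and Trial status dates the first participant to 2 January 2020. Keep the 108 patients.

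The cost is some wording and a recalculation. The downside is a less favourable stated power for the key contrast.

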**Discussion:**

The results of this trial will allow us to compare the difference in efficacy between stuck-moving needle acupuncture MTrP with that of common acupuncture treatments. The findings from this trial will be published in the peer-reviewed journals.

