## Discussion

Idiopathic frozen shoulder is a common and painful disease with a long course. Although the disease has a certain tendency of self-healing, it lasts for prolonged time. It is difficult for the affected side of shoulder joint to fully return in normal function. If it does not function properly, it may lead to functional disability and directly affects the day-today life of the patient. Worldwide, chronic shoulder pain is considered as one of the indications as most amenable to treat with acupuncture [26, 27]. According to the results of previous systematic reviews and clinical studies [28, 29], acupuncture as a main treatment for frozen shoulders has a good therapeutic effect, and the key factors affecting the effect of acupuncture are acupuncture techniques and acupuncture sites. The acupuncture method used in this study is stuck-moving needle acupuncture therapy. The acupuncture sites are selected from the local MTrp of the shoulder joint. At present, there is no significant clinical research which can prove whether the combination of the stuck-moving needle and MTrp is better than the combination of ordinary acupuncture and the acupuncture point. Our pilot study showed that stuck-moving needle used for acupuncture MTrp was effective in improving the pain and movement limitation of the patients with idiopathic frozen shoulder. However, this study was a single case observation in a single center, without a control group. Therefore, in our study, we designed a multi-center, large-sample, randomized controlled clinical trial to evaluate the efficacy and safety of stuck-moving needle acupuncture the MTrp in improving pain and range of motion in patients with idiopathic frozen shoulder. The ultimate aim of the study was to select an effective acupuncture therapy for patients with idiopathic frozen shoulder.

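### The stated power of 0.931 at 30 per group does not follow from the plan's own inputs, and the lead comparison (stuck-moving needle versus common acupuncture) has only 46% power at that size

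*Protocol article*

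**What the plan says.** Group A is stuck-moving needling of trigger points, group B common acupuncture and group C physical exercise, which A and B also receive.

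The Sample size estimation section gives all the inputs. From an earlier published study, the VAS change in the "general acupuncture group was 4.7, with a standard deviation of 1", and in the "functional exercise group was 3.5, with a standard deviation of 1". From the team's own pilot, VAS with "stuck-moving needle acupuncture dropped by 5.2 and the standard deviation was 1.06". The design is "three groups and the sample size as 1:1:1". The method is an F-test from single-factor ANOVA in SAS 9.4, with alpha 0.05 and target power 0.9. The result is then given: "The results showed that the test power was 0.931, and the number of samples in each group was not less than 30". An allowance for loss raises 30 to 36 per group, 108 in total. No power or sample size is given for any pair of groups.

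The article puts A versus B first. The Discussion part of the Abstract says the results will allow the authors to "compare the difference in efficacy between stuck-moving needle acupuncture MTrP with that of common acupuncture treatments". The Abstract's Background, the section on the rationale for the intervention and the main Discussion say the same. Comparison with exercise is also an aim, named second in the rationale for the trial design.

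**The concern.** Two things look wrong.

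First, the planned means differ by up to 1.7 points with SDs of about 1. An omnibus F-test with 90 patients should then have power of practically 1, so 0.931 cannot belong to 30 per group on these inputs.

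Second, an omnibus test can be nearly certain to reject because one arm stands apart. Here the exercise arm does. The planned gap between the two needling arms is about half an SD, and the omnibus power says almost nothing about detecting it.

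The risk is in interpretation. If the planning values are true, a non-significant A-B result is more likely than not with 30 evaluable per group. Anyone who believes the trial had more than 90% power for its question would read that result as evidence that the needling method makes no difference.

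**Working it through.** **Inputs** (all from Sample size estimation): means 5.2 (A), 4.7 (B), 3.5 (C); SDs 1.06, 1, 1; equal groups; alpha 0.05. The Statistical analysis section makes tests two-sided.

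**1. Trying to reproduce 0.931.**
- Grand mean = (5.2 + 4.7 + 3.5)/3 = 4.467.
- Sum of squared deviations = 0.538 + 0.054 + 0.934 = 1.527.
- Pooled SD = √[(1.06² + 1 + 1)/3] = 1.020.
- Effect size f = √(1.527/3)/1.020 = 0.699.
- Noncentrality λ = n × 1.527/SD². At n = 30 with the pooled SD, λ = 44.0. The critical value is F(2, 87) = 3.10. Power is the upper tail of the noncentral F.

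| SD used | n = 10 | n = 11 | n = 12 | n = 30 |
|---|---|---|---|---|
| 1.00 | 0.921 | 0.946 | 0.964 | 0.99999 |
| 1.02 (pooled) | 0.910 | 0.937 | 0.957 | 0.99999 |
| 1.06 | 0.887 | 0.918 | 0.942 | 0.99996 |

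The stated figure is not reproduced at 30 per group. A power of 0.931 falls between 10 and 11 per group with SD 1.00 or the pooled SD, and between 11 and 12 with SD 1.06. Keeping 30 per group and solving for the SD gives 1.77. Tightening alpha to 0.01 still leaves at least 0.9995 at 30 per group. A total of about 30 may have been reported as a per-group number (10 per group gives 0.921 with SD 1), but the text does not confirm this.

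**2. Where the omnibus power comes from.** The sum of squares splits exactly into two contrasts:
- A versus B: 0.5²/2 = 0.125.
- Mean of A and B versus C: (2/3) × (4.95 − 3.5)² = 1.402.

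Together they make 1.527. A versus B contributes 0.125/1.527 = 8%, and needling versus exercise contributes 92%. As a check, if the exercise mean is moved to 4.95, midway between A and B, the omnibus power at 30 per group falls to 0.367.

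**3. Power for A versus B.**
- SD = √[(1.06² + 1²)/2] = 1.030, so d = 0.5/1.030 = 0.485.
- Noncentrality = 0.485 × √(n/2): 1.879 at n = 30 and 2.059 at n = 36.

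| | 30 per group | 36 per group |
|---|---|---|
| Two-sample t-test, unadjusted | 0.456 | 0.528 |
| ANOVA contrast (three-group error) | 0.467 | 0.540 |
| Bonferroni over three pairs | 0.287 | 0.353 |

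About 91 per group would be needed for 90% power. For comparison, at 30 per group A versus C has power above 0.9999 and B versus C has 0.995.

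**4. Precision for A versus B at 30 per group.**
- Standard error = 1.030 × √(2/30) = 0.266.
- Expected 95% CI half-width = 2.002 × 0.266 = 0.53, slightly wider than the planned effect of 0.5.
- Detectable difference: 0.76 at 80% power, 0.88 at 90%.
- At 36 per group the half-width is 1.994 × 1.030 × √(2/36) = 0.48.

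**The case against.** The case for leaving the text alone has four parts.

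- **The error is in the safe direction.** The stated power is too low for the stated n, so the test actually sized is over-powered. This is true of the omnibus test and of both comparisons with exercise. It does not help A versus B.
- **The sizing matches the analysis.** The article says openly that it sized an ANOVA F-test, the Statistical analysis section names ANOVA for the primary outcome, and nowhere is 90% power claimed for A versus B. This stands as a description. But a significant F-test would not answer the question the article puts first, and the only power figure printed is one a reader will attach to that question.
- **A versus B is not the only aim.** Study design speaks of comparing three treatment options, and the Discussion describes two control groups. This also stands: the comparisons with exercise are legitimate aims and are well powered. A versus B is still the lead question.
- **The conclusion rests on the full analysis set with LOCF, so the analysed number should be near 36.** That gives 0.528 rather than 0.456, and unadjusted power passes one half at 34 per group. So the statement that a non-significant result is more likely than not applies at 30 evaluable, not at 36. The fair summary is 46% to 53%, still far from 90%, and any multiplicity adjustment lowers it.

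**Conclusion.** The concern holds, and the section must be corrected. On the plan's own inputs the omnibus power at 30 per group is 0.99996 to 0.99999, not 0.931. The power for A versus B is 0.456 at 30 evaluable per group and 0.528 at 36.

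These figures assume the planned means and SDs are true, an unadjusted two-sided 5% test, and VAS change as the outcome. They say nothing about range of motion, which is also primary but was not used in the sizing. The planned difference of 0.5 is itself soft: it sets a published value for B against the team's pilot value for A, and the article says of the pilot that "this study was a single case observation in a single center, without a control group". A larger true difference would raise the power, and a smaller one would lower it. Neither would reconcile 0.931 with the printed inputs.

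**What to change.** In Sample size estimation, replace the sentence reporting 0.931 with figures that follow from the inputs:

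- Omnibus one-way ANOVA: power above 0.99 at 30 per group. Because the same inputs reach 0.9 with 10 to 11 per group, say why 30 was chosen, or show the SAS inputs if they differ from those printed.
- A versus B, difference 0.5, SD 1.03, unadjusted: power 46% with 30 evaluable per group and 53% with 36.
- A versus B at 30 per group: detectable difference 0.76 at 80% power, expected 95% CI half-width 0.53.
- A versus C and B versus C: power above 99%.

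Add that a non-significant A-B result will be reported with its confidence interval as inconclusive, not as equality of the two needling methods.

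The cost is a few sentences, plus a less favourable stated power for the lead question. No extra patients and no change of design or treatment are asked for.
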